## Abstract

**Background:**

Metabolic syndrome (MetS) is increasingly present in breast cancer survivors, possibly worsened by cancer-related treatments, such as chemotherapy. MetS greatly increases risk of cardiovascular disease and diabetes, co-morbidities that could impair the survivorship experience, and possibly lead to cancer recurrence. Exercise has been shown to positively influence quality of life (QOL), physical function, muscular strength and endurance, reduce fatigue, and improve emotional well-being; however, the impact on MetS components (visceral adiposity, hyperglycemia, low serum high-density lipoprotein cholesterol, hypertriglyceridemia, and hypertension) remains largely unknown. In this trial, we aim to assess the effects of combined (aerobic and resistance) exercise on components of MetS, as well as on physical fitness and QOL, in breast cancer survivors soon after completing cancer-related treatments.

**Methods/Design:**

This study is a prospective randomized controlled trial (RCT) investigating the effects of a 16-week supervised progressive aerobic and resistance exercise training intervention on MetS in 100 breast cancer survivors. Main inclusion criteria are histologically-confirmed breast cancer stage I-III, completion of chemotherapy and/or radiation within 6 months prior to initiation of the study, sedentary, and free from musculoskeletal disorders. The primary endpoint is MetS; secondary endpoints include: muscle strength, shoulder function, cardiorespiratory fitness, body composition, bone mineral density, and QOL. Participants randomized to the Exercise group participate in 3 supervised weekly exercise sessions for 16 weeks. Participants randomized to the Control group are offered the same intervention after the 16-week period of observation.

**Discussion:**

This is the one of few RCTs examining the effects of exercise on MetS in breast cancer survivors. Results will contribute a better understanding of metabolic disease-related effects of resistance and aerobic exercise training and inform intervention programs that will optimally improve physiological and psychosocial health during cancer survivorship, and that are ultimately aimed at improving prognosis.

**Trial registration:**

NCT01140282; Registration: June 10, 2010

## Background

Recent estimates show that within the U.S. there are more than 2.4 million breast cancer survivors with a 5-year survival rate of 88.6% [1]. These survivors are at an increased risk of cancer recurrence, comorbidities such as diabetes, osteoporosis and cardiovascular disease, and premature death [2,3]. They also have special needs as a consequence of the adverse effects associated with common treatments, such as surgery, chemotherapy, radiation therapy, and endocrine therapy. One important consequence of these adverse effects is a profound decline in physical activity [4]. This is of particular concern as physical activity is thought to lower the risk of cancer recurrence and mortality [5]. Studies of survivors 6–12 months following treatment describe individuals with decreased cardiorespiratory function, muscle strength, bone mineral density, and physical well-being [6,7]. In addition, these survivors experience fatigue, depression, anxiety, and weight gain [8-10]. These effects of decreased physical activity appear to have more profound effects on cardiovascular and psychosocial health in those undergoing radiation and some forms of chemotherapy [3,11]. While the effects between decreased physical activity and factors of overall well-being has been established in moderate and long-term survivors [12-15], less information is available with regards to ‘early’ (0–6 months post-treatment) survivors.

In 2012, the American Cancer Society released guidelines for cancer patients and survivors promoting physical activity to improve cancer outcomes [16], emphasizing the beneficial effects of exercise for the health of breast cancer survivors. Not only has physical activity been associated with decreased breast cancer risk [17-19], it has also been shown to be beneficial for breast cancer survivors. For example, aerobic exercise has been found to improve cardiorespiratory function in survivors 6 months to 5 years post-treatment [12,13,20,21], which is particularly important for survivors who have had cardiac damage from chemotherapy. Resistance exercise has been found to increase muscle strength [7,14,22,23], which subsequently reduces injuries and improves balance. Additionally, combined (aerobic and resistance) exercise programs result in improvements in cardiorespiratory function and muscle strength in breast cancer survivors [24-26]. Combined exercise involves both resistance and aerobic exercises in a single session and therefore, is effective in improving cardiovascular, musculoskeletal, and psychological health.

Current evidence suggests that breast cancer treatments, such as chemotherapy, lead to weight gain and increased adiposity, fatigue, physical inactivity, and negative alterations in components of metabolic syndrome (MetS) [4,10,27]. Metabolic syndrome (MetS), which is associated with increased risk of cardiovascular diseases and type 2 diabetes (6), is a cluster of risk factors including visceral adiposity, hyperglycemia, low serum high-density lipoprotein cholesterol, hypertriglyceridemia, and hypertension [28]. MetS is highly prevalent and present in at least 25% of American and European adults [29]. Therefore, despite high breast cancer survival rates, many breast cancer survivors are at risk of and may experience mortality from diabetes and cardiovascular disease, which can be modified by lifestyle interventions [30,31]. Obese postmenopausal breast cancer survivors receiving adjuvant hormone therapy present with MetS and elevated levels of C-reactive protein, placing them at a higher risk for cardiovascular and metabolic diseases [27,32,33]. Premenopausal breast cancer patients experience detrimental effects such as increased body mass index (BMI) and central obesity from adjuvant chemotherapy potentially contributing to MetS [34]. Chemotherapy in premenopausal breast cancer patients frequently induces premature menopause, which is associated with increases in body fat, cholesterol, and triglycerides [34,35]. These changes may contribute to earlier development of cardiovascular disease or type 2 diabetes among women already at risk or to increased risk among those not already predisposed to these diseases [28].

Treatment and management of MetS mainly consists of symptomatic drug treatments of the syndrome’s individual components [36]. Candidate drugs that reduce hyperglycemia may have additional metabolic benefits. Examples are metformin, currently being evaluated in a large randomized adjuvant trial for early stage breast cancer [37], PPARγ agonists, GLP-1 agonists, and DPP-4 inhibitors [36,38]. However, since lifestyle factors such as physical activity, dietary intake, and smoking habits affect the risk of developing MetS, it is important and possibly preferable to target lifestyle factors to prevent the onset of metabolic-related diseases in breast cancer survivors. The few studies that have examined the effects of exercise training on particular components of MetS in postmenopausal breast cancer survivors have shown reduced insulin levels and waist circumference, but no change in insulin resistance, fasting glucose, or body weight [39,40]. Some of these results are promising and emphasize the need for additional studies in this area. Studies of premenopausal survivors will be particularly important. Given that chemotherapy induces many of the components of MetS, an effort to offset potential treatment side effects can greatly benefit breast cancer patients.

This trial is a prospective, randomized controlled trial (RCT) in breast cancer survivors following chemotherapy and/or radiation treatments exploring the effects of a 16-week supervised progressive combined (aerobic and resistance) exercise intervention on components of MetS (visceral adiposity, glucose, high-density lipoprotein cholesterol, triglycerides, and blood pressure), as well as muscular strength, cardiorespiratory fitness, and body composition.

### Objectives

The primary objective of this trial is to determine the effects of a 16-week combined exercise intervention on components of metabolic syndrome (MetS) including waist circumference, blood pressure, fasting glucose, HDL, triglycerides, and glucose, compared to a usual care control group among breast cancer survivors. Secondary objectives are to determine the effects of exercise on cardiorespiratory fitness, muscle strength, body composition, quality of life, shoulder strength and range of motion (ROM), and serum levels of insulin, C-reactive protein, and glycosylated hemoglobin (HbA1c). Safety and feasibility of the supervised exercise program will be evaluated, and the sustainability of the effects will be assessed.

## Methods/Design

### Study design

This RCT targets women with stage I-III breast cancer following radiation and/or chemotherapy treatments. After obtaining written consent, participants are randomized to a supervised combined (aerobic and resistance) exercise program over 16 weeks (Exercise Group) and usual care (Control Group; see Figure 1). Endpoints are assessed at baseline (T1), after the end of the 16-week intervention (T2), and 12 weeks post-intervention (Exercise Group only; T3; see Figure 2).

**Figure 1 F1:**
[figure not shown]
**Study design.** Endpoints are assessed at baseline (T1), after the end of the 16-week intervention (T2), and 12 weeks post-intervention (Exercise Group only; T3).

**Figure 2 F2:**
[figure not shown]
Study flow.

To enhance participation rate and maintain high compliance to the intervention scheme, participants in the Control group are offered the exercise program following the study period. Participants in the Exercise group are supervised by a certified exercise specialist to ensure a tailored, personalized program is executed. The exercise intervention is based on a previously utilized program deemed safe and effective in breast cancer survivors [40].

This study was approved by the Institutional Review Board of the University of Southern California (HS-12-00141) and is registered at ClinicalTrials.gov (NCT01140282).

### Participant selection

This trial includes women with histologically confirmed Stage I-III primary breast cancer who have recently completed all cancer-related treatments and who do not have any contraindications for moderate exercise. Inclusion and exclusion criteria are provided in Table 1.

**Table 1 T1:** Inclusion and exclusion criteria

**Inclusion criteria**	**Exclusion criteria**
• Women with primary breast cancer, stage I-III	• History of chronic disease (i.e., diabetes, uncontrolled hypertension, thyroid disease)
• ≥ 18 years of age	• Weight reduction > 10% within past 6 months
• Have undergone lumpectomy or mastectomy	• Metastatic disease
• Have completed neoadjuvant/adjuvant chemotherapy and/or radiation therapy	• Planned reconstructive surgery with flap repair during trial or follow-up period
• Initiate exercise program (if randomized to that arm) within 24 weeks of therapy completion	• Cardiovascular, respiratory, or musculoskeletal or joint problems that preclude moderate physical activity
• BMI ≥ 25 kg/m^2^ or body fat > 30%	
• Currently participates in < 60 minutes of physical activity per week	
• May use adjuvant endocrine therapy if use will be continued for duration of study period	
• Nonsmokers (No smoking during previous 12 months)	
• Willing to travel to USC	
Able to provide physician clearance to participate in exercise program	
• Women of all racial and ethnic backgrounds will be included in the study enrollment process	

### Recruitment and randomization

All eligible breast cancer patients scheduled for chemotherapy and/or radiation at the USC Norris Comprehensive Cancer Center (NCCC) or Los Angeles County Hospital are briefly informed about the trial during their medical oncology or surgical oncology appointments. If interested, patients are then informed in detail about the trial by the study principal investigator and inclusion/exclusion criteria are verified. For each patient recruited into the study, written informed consent is obtained prior to performing randomization or outcome measure testing. Upon written informed consent, the patient is randomly assigned to either the Exercise or Control groups, and scheduled for the baseline visit, which should be within 0–24 weeks of completing chemotherapy and/or radiation. Randomization (intervention assignment) is done by the Clinical Investigation Support Office (CISO) at the USC NCCC; study investigators contact CISO once the participant has signed the informed consent and is registered. To randomly assign the intervention arm to patients, 2 randomization lists are prepared in advanced to accommodate the stratification: one for pre-menopausal participants and one for post-menopausal participants, based on their menopausal status at time of cancer diagnosis. The randomization is based on a permuted block design with block size of 10. Stratification is used in the randomization process, as we expect menopausal status to have a major influence on our study outcomes. To prevent possible bias, study personnel involved in the recruitment do not have access to the randomization lists. Conversely, the biostatistician does not have influence on the recruitment procedure.

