**Secondary endpoints**				
Cardiorespiratory fitness	4-minute walk test	X	X	X
Muscle strength	10-RM- leg extension, leg flexion, chest press, seated row	X	X	X
Body composition	DEXA, weight, height, lean mass, % body fat, hip circumference	X	X	X
Quality of life	SF-36, FACT-B, CES-D	X	X	X
Shoulder strength	Muscle force for SE and ER	X	X	X
Shoulder ROM	Measured with goniometer at 90° ER, forward flexion,	X	X	X
Upper limb musculoskeletal disorder assessment	DASH, PSS	X	X	X
Biomarkers- inflammation & endocrine function	Analyzed in peripheral blood	X	X	X

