#### Cardiopulmonary fitness

A single-stage submaximal treadmill test is used to estimate maximal oxygen uptake [46]. Cardiopulmonary fitness testing is well established in cancer patients and recommendations for testing procedures as well as safety guidelines in clinical trials with cancer populations have been well defined [47]. The procedure is also used to exclude exercise-contraindicating cardiac impairments. Participants are instructed to walk so they are able to talk while walking at a speed of 2.0, 3.0, 4.0, or 4.5 mph on a treadmill (Desmo Woodway, Waukesha, WI) for 4 minutes at a 5% grade and heart rate is measured at the end of the test. Using HR, speed, age and gender, maximal oxygen uptake is calculated using the specific formula that applies to this test.

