### Data analysis

The main intervention effect will be assessed on the basis of a comparison between exercisers and controls as defined at randomization, regardless of exercise adherence, i.e., according to intent-to-treat principle. A 2 (group) × 2 (time) repeated measures analysis of variance (ANOVA) will be used to examine changes in MetS score and for each individual component of MetS. Stratification by type of therapy (i.e., surgery, chemotherapy, radiation) may result based on therapy regimens completed by enrolled subjects. Similar analyses as for MetS will also be performed for the secondary endpoints. Correlation analyses will be used to examine the relationship between changes of the various measured endpoints. Regression analyses regarding the repeated measurement design (T1, T2, T3) will be applied to investigate the association between exercise intervention, MetS, cardiopulmonary fitness, muscle strength, body composition, and the QOL dimensions. The influence of other potential confounding factors, such as age, clinicopathologic characteristics, and comorbidities will be explored and accounted for in the analysis. In addition, change in physical activity behavior post intervention will be explored for the follow-up time points using descriptive analysis.

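### Allocation precedes the baseline visit, so T1 readings, some exclusions and one arm-specific criterion fall after randomisation

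*Protocol article*

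**What the plan says.** All references are to the protocol article.

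- **Order of events.** Recruitment and randomization: "Upon written informed consent, the patient is randomly assigned to either the Exercise or Control groups, and scheduled for the baseline visit". The same section says that "written informed consent is obtained prior to performing randomization or outcome measure testing", which puts consent ahead of both steps but does not put testing ahead of allocation. The Clinical Investigation Support Office (CISO) is contacted for the assignment after consent and registration. Study design likewise moves straight from consent to randomisation.
- **Screening before consent.** The same section says that, when the trial is explained in detail, "inclusion/exclusion criteria are verified".
- **A T1 test that also excludes.** Cardiopulmonary fitness says of the submaximal treadmill test: "The procedure is also used to exclude exercise-contraindicating cardiac impairments". Table 3 lists it ("Cardiorespiratory fitness 4-minute walk test") at T1, T2 and T3.
- **Body fat.** Table 1 admits women with a BMI of at least 25 kg/m² "or body fat > 30" per cent. Body composition describes body fat only as a DXA or bioimpedance measurement, and Table 3 schedules body composition at T1.
- **A criterion conditional on allocation.** Table 1, inclusion: "Initiate exercise program (if randomized to that arm) within 24 weeks of therapy completion".
- **Analysis.** Data analysis promises "a comparison between exercisers and controls as defined at randomization, regardless of exercise adherence", using a group-by-time repeated measures ANOVA with baseline as one of the two times.

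**The concern.** The primary outcome is change from T1 to week 17, so anything that allocation can do to T1, or to who has a T1, enters the primary comparison directly. There are three routes.

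1. **Measurement.** If the participant or the tester knows the arm at T1, readings that depend on an observer, on effort or on self-report can be affected. Waist and blood pressure are two of the five scored components. Strength, dynamometry and the questionnaires are secondary examples.
2. **Missing baselines.** A woman who withdraws, or is excluded, between allocation and T1 has no change score. Losses at this stage may differ by arm, because the woman may have just learned whether she will train now or wait.
3. **Arm-specific eligibility.** A criterion that applies only after allocation to exercise can be failed in one arm and not in the other.

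More participants would not cure any of these. They concern bias, not precision.

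**Working it through.** **Step 1. What falls after allocation.**

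| Item | When it is settled | Can it follow allocation? |
|---|---|---|
| Most Table 1 criteria | Verified before consent | No |
| T1 waist, blood pressure, bloods, fitness, questionnaires | Baseline visit | Yes |
| Treadmill exclusion for cardiac impairment | Treadmill test, scheduled at T1 | Yes |
| Body fat criterion | Only decides for BMI below 25; source of the reading not stated | Possibly |
| Start of exercise within 24 weeks | After allocation, Exercise arm only | Yes, by construction |

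**Step 2. The time-since-therapy statements side by side.**

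| Place | Limit | Clock stops at | Arms |
|---|---|---|---|
| Abstract, Methods/Design | 6 months | Initiation of the study | Both |
| Table 1 | 24 weeks | Start of exercise | Exercise only |
| Recruitment and randomization | 0–24 weeks, worded as a should | Baseline visit | Both |
| Discussion, on early survivors | 0–6 months | Study entry | Both |

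These name four different end events and two limits (24 weeks = 24 × 7 = 168 days; six months is about 182). Take a woman whose baseline visit falls at week 24. She meets the baseline window in either arm. If allocated to exercise and started any later, she fails Table 1. If allocated to control, she cannot fail it. The asymmetry is therefore real but confined to women near the limit.

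**Step 3. How a T1 error enters the result.** Change = T2 − T1, and the group-by-time term compares mean change between arms. An average error e in T1 confined to one arm moves the contrast by −e, undiluted. The score is built from cut-offs (waist above 35 inches, blood pressure above 130/85). If a fraction p of one arm is reclassified on one component at T1, that arm's mean score moves by p points on the 0–5 scale. The document gives nothing from which to estimate p.

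**Step 4. The plan's own figure.** Inputs from Sample size: difference 2.6, SD 4.0 (insulin, μU/ml), two-sided 5%, 80% power, t-test. Equal arms are assumed.
- Standardised difference = 2.6/4.0 = 0.65.
- The t-test needs 38.14, so 39 per arm or 78 in total, against 80 stated. At 40 per arm, power is 81.9%.
- 80/(1 − 0.20) = 100, as stated.

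Reordering the visits leaves all of this unchanged.

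**Step 5. Illustrations only; every loss rate here is assumed.**

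*(a) Withdrawal between allocation and T1.* Suppose 4 of 50 controls and 1 of 50 exercisers leave, and those lost would have changed by 1 SD more or less than the rest. Shift in an arm's mean = (lost/50) × 1 SD: 4/50 = 0.08 SD for controls, 1/50 = 0.02 SD for exercisers. Net shift in the contrast: 0.08 − 0.02 = 0.06 SD if the losses run in the same direction, 0.08 + 0.02 = 0.10 SD if opposite. Against 0.65 SD that is 0.06/0.65 = 9% to 0.10/0.65 = 15%.

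*(b) Exclusion from the Exercise arm alone.* Suppose a fraction f is removed from the upper tail of a normal trait whose correlation with the baseline outcome is ρ. The baseline mean shifts by ρ·φ(z)/(1 − f), where z is the (1 − f) normal quantile.

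| f | Shift, ρ = 0.3 to 1.0 (SD) | As share of 0.65 SD | Power, 40 v 40(1 − f) |
|---|---|---|---|
| 5% | 0.03–0.11 | 5–17% | 80.9% |
| 10% | 0.06–0.19 | 9–30% | 79.7% |
| 20% | 0.11–0.35 | 16–54% | 77.1% |

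This is a shift in the baseline mean. How much of it reaches the change contrast depends on how change relates to baseline, which is not given. The 0.65 SD benchmark is for insulin, a secondary outcome; no SD for the metabolic syndrome score is stated.

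**The case against.** The case on the other side is substantial, and much of it stands.

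- **Knowledge of the arm at T1 is not documented.** A reader might infer that T1 is taken with the arm known to participant and staff. The article does not say when the arm is disclosed or whether testers know it. What stands is that T1 follows allocation and no concealment at that visit is described.
- **Screening does precede allocation.** Criteria are verified before consent, Table 1 separately excludes cardiovascular problems that preclude moderate activity, and physician clearance is required. The treadmill test is a residual check, taken in both arms. An exclusion decided blind to allocation and by the same rule in both arms would not bias the comparison. The exposure arises only if the decision, or attendance, depends on the arm.
- **Body fat is a narrow route.** It decides eligibility only below BMI 25, and nothing says that the reading comes from the T1 scan.
- **The 24-week rule has a counterpart for both arms.** The baseline window limits the asymmetry, though it governs the visit and not the start of exercise.
- **Visit order does not contradict intention to treat.** A reader might see a conflict with the Data analysis section. There is none in the order itself, and nothing says that late starters or women excluded at T1 are dropped. How such women are handled may be left to an analysis plan that is not shown.
- **There are safeguards.** Recruiting staff cannot see the lists, three of the five components are blood assays run on stored serum after the last participant finishes, and controls are offered the programme later, which may limit their losses.

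**Conclusion.** The point holds in a limited form. By the article's own sequence T1 is taken after allocation. A test used for exclusion, and possibly body fat for some women, falls at that same visit. One inclusion criterion can be failed only in the Exercise arm. Together these leave a route by which baseline values and the set of women with a baseline can depend on allocation, in a trial whose primary outcome is change from baseline.

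It would go too far to say that randomisation no longer protects the comparison. Allocation itself is concealed from recruiters, most eligibility is settled beforehand, and the asymmetry in the time window touches only women near the limit.

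The size of any bias cannot be computed from the document. The illustrations above rest wholly on assumed losses and on an insulin benchmark, and should not be read as estimates for the metabolic syndrome score. The case for the change is that it closes the route at almost no cost, not that a given bias has been shown.

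**What to change.** 1. **Reorder.** After consent, complete T1 (bloods, blood pressure, waist, body composition, treadmill test, questionnaires), confirm eligibility, and only then contact CISO for the allocation.
2. **Reconcile the windows.** The Abstract, Table 1, Recruitment and randomization, and the Discussion should carry one time-since-therapy criterion, with one defined end event, judged at randomisation in the same way for both arms. Which limit applies is for the investigators to settle.
3. **For women already randomised under the present order,** report exclusions and withdrawals between allocation and T1 by arm, with reasons.

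**Cost.** A procedural amendment. It needs no extra visit, test or participant, and the figures of 80 evaluable and 100 recruited stand. Allocation moves from the time of consent to the end of T1, and women found ineligible at T1 are then screening failures and not post-randomisation losses.

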### Participant-reported outcomes

#### Physical activity assessments

Physical activity history is assessed at baseline using an interviewer-administered physical activity questionnaire [53]. Throughout the duration of the study period, weekly 7-day physical activity logs [54] are completed by all participants and returned to the PI by mail for the Control group.

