### Sample size

The primary aim is to compare changes in overall MetS scores from baseline to week 17 between the Exercise and Control groups. Since MetS has not been investigated in breast cancer survivors at the time of project initiation, we chose to calculate sample size using changes in insulin following exercise in breast cancer survivors. This project is designed to detect a treatment effect based on insulin results with 80% statistical power at a 5% level of statistical significance. Ligibel et al. assessed insulin levels before and after a 16-week exercise intervention in breast cancer survivors [40]. Using their results, a sample size of 80 participants would detect a difference in mean insulin levels of 2.6 μU/ml assuming that the common standard deviation is 4.0 μU/ml using a two group t-test with two-sided 5% level of statistical significance. Therefore, to allow for a 20% maximum withdrawal rate, 100 participants will be recruited, of whom 50 will be premenopausal and 50 postmenopausal.

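### One fixed block size of 10 in an unmasked trial: withholding the lists does not stop deduction, and up to one assignment in six could be known before consent

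*Protocol article*

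**What the plan says.** Under Recruitment and randomization the article gives the allocation method: "The randomization is based on a permuted block design with block size of 10". Two lists are prepared, "one for pre-menopausal participants and one for post-menopausal participants". They are not split by recruiting hospital. Staff who recruit are kept away from the lists.

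The same section describes contact before consent: "patients are then informed in detail about the trial by the study principal investigator and inclusion/exclusion criteria are verified". Assignment comes later, through the Clinical Investigation Support Office (CISO): "study investigators contact CISO once the participant has signed the informed consent and is registered".

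Under Physical activity assessments, the weekly activity logs are "completed by all participants and returned to the PI by mail for the Control group".

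Under Sample size, "100 participants will be recruited, of whom 50 will be premenopausal and 50 postmenopausal". Study design and Exercise intervention set one-on-one supervised training against usual care, so participants and trainers know the arm.

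**The concern.** Keeping the list secret and keeping the next assignment unpredictable are different protections. The article provides the first. With open treatment and every block the same size, past allocations carry information about the next one: once one arm has its full share of a block, the rest of that block is determined.

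The people placed to use this information are close to enrolment. Investigators inform candidates and later obtain their assignments, and the principal investigator learns who is in the Control group from the mailed logs.

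Several entry criteria in Table 1 leave room for judgement: weekly activity below 60 minutes, physician clearance, and joint or cardiovascular problems that would rule out moderate activity. The window of up to 24 weeks after therapy leaves some room to delay a candidate. If the next arm were known, keener or fitter women could be steered toward one arm. The arms would then differ at baseline in motivation and fitness. The intention-to-treat comparison in Data analysis does not correct selection that happens before randomisation, and adjustment for age, clinicopathologic characteristics and comorbidities would not capture motivation.

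**Working it through.** The article gives no figure for predictability, so there is none to reproduce. The check uses its design inputs.

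**Inputs**
- Block size 10, fixed (Recruitment and randomization).
- Two lists, by menopausal status (same section).
- 100 women, 50 per stratum (Sample size): 50/10 = 5 complete blocks per list, 10 in all.
- Allocation 1:1, so 5:5 per block. *This is an assumption; the ratio is not stated.* It fits the sample size section, which sizes the trial "using a two group t-test with two-sided 5% level of statistical significance". With 40 per arm, a difference of 2.6 and an SD of 4.0 (standardised effect 2.6/4.0 = 0.65), power is 81.9%, against the 80% planned; and 100 × (1 − 0.20) = 80 evaluable.

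**Assignments known with certainty**

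For a block with *m* per arm, the expected number of assignments made after one arm is full is 2*m*/(*m* + 1).
- *m* = 5: 10/6 = 1.67 per block, a share of 1.67/10 = 16.7%, exactly one in six.
- Enumerating all C(10,5) = 252 sequences gives the same value.
- Per stratum: 5 × 1.67 = 8.3 of 50. Overall: 10 × 1.67 = 16.7 of 100.
- The last assignment in each block is always certain.

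The range runs from 0 of 100 (nobody tallies) to 16.7 of 100 (complete tally in both strata, block size known). The 1:1 assumption does not drive the result: a 6:4 block would give 6/5 + 4/7 = 1.77 per block.

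**What the tally must contain**

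Totals by stratum and arm are enough. Suppose 18 women in a stratum have been randomised, 10 to exercise and 8 to control. The first block took 5 and 5, so the current block holds 5 and 3, and the next two assignments must be control.

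**Best guessing**

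Always guessing the arm that is behind gives *m* + (4^*m*/C(2*m*,*m*) − 1)/2 correct guesses per block. For *m* = 5 this is 5 + (1024/252 − 1)/2 = 6.53 of 10, or 65%, against 50% by chance.

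**Alternatives**

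The fixed-block rows are exact. The varied rows are simulated for 50 women per list, with an observer who keeps a full tally and knows the set of possible sizes.

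| Block sizes | Certain in advance | Best-guess success |
|---|---|---|
| 4 fixed | 33% | 71% |
| 6 fixed | 25% | 68% |
| 8 fixed | 20% | 67% |
| **10 fixed (current)** | **16.7%** | **65%** |
| 4, 6, 8 varied | 2.4% | 68% |
| 6, 8, 10 varied | 1.7% | 66% |
| 4, 6, 8, 10 varied | 1.2% | 67% |
| 8, 10, 12 varied | 1.4–1.5% | 65% |

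Varying the size removes nearly all certainty. It does not remove probabilistic guessing, and small blocks make guessing slightly easier.

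**The case against.** The design already has real protections. Assignment is central and follows signed consent and registration. There are only two strata, and 10 is a large block: fixed blocks of 4 or 6 would leave 33% or 25% of assignments certain. The 24-week limit restricts how long a candidate can be held back. All of this stands, and it keeps the weakness modest. None of it stops deduction from past allocations.

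It can also be objected that the conditions behind one in six are not shown to hold. That is correct. A reader might infer more than the article supports:
- *That recruiters know the block size.* It is printed in the article, but nothing says that recruiting staff were told it.
- *That the principal investigator personally checks eligibility and sees every allocation.* The eligibility sentence is passive and names no one. The logs "returned to the PI by mail for the Control group" reveal Control membership; a complete tally by stratum is plausible but not documented.
- *That this is a single-centre trial.* Two hospitals recruit, and first contact is spread over several clinics. The calculation is unaffected, because both hospitals feed the same two lists.
- *That the 65% guessing rate shows harm from fixing the size.* It does not. Varied sizes of 4, 6, 8 and 10 give about 67%. The case for change rests on the certain assignments alone.

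**Conclusion.** The point holds as a design weakness of limited size. The stated safeguard protects the lists but not the next assignment. In an open trial with fixed blocks of 10, up to one assignment in six (about 17 of 100) could be certain before consent. This figure assumes 1:1 allocation, knowledge of the block size and a complete tally in each stratum; with less information the share is lower. The stronger conclusion, that enrolment was steered or that the arms differ because of it, has no support in the article.

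**What to change.** For participants not yet randomised, CISO should generate the remaining part of each list with randomly varied block sizes that are no smaller on average than now, for example 8, 10 and 12, and should not disclose the sizes to investigators. The sentence in Recruitment and randomization should be amended to say that block sizes vary at random within each menopausal stratum and are held by CISO. The allocation ratio can be stated in the same place. Sizes such as 4 and 6 should be left out, for the reason shown in the table.

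The cost is regenerating two lists at an office that already runs the randomisation, plus a slight possible imbalance at the end of each stratum. If enrolment is already complete, the lists cannot be changed; the trial report should then state the block size and show baseline balance, including by position within block.
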